### Participants

Eligible participants will be adults with stage I, II, and III cancer who were treated with curative intent and had completed their main medical treatment (surgery, radiotherapy, or chemotherapy). Moreover, participants will have to express a need for psychological care, and they will have low or undefined meaning in life (scores below 105 on the Purpose in Life test) (31). The recruitment will be carried out by an oncologist and two clinical psychologists with more than 10 years of experience in cancer care. The sample will be recruited from the Valencian Oncology Institute in Valencia from January to June 2022. Thus, it is an ongoing study.

The exclusion criteria will be: (1) participants who are currently receiving another psychological or psychiatric treatment; (2) the diagnosis of a serious mental disorder (schizophrenia, substance dependence, dementia, or cognitive impairment).

### Procedure

Cancer survivors who have been treated at the Valencian Institute of Oncology will be offered the opportunity to participate in the study. Once they have signed the informed consent, a clinical psychologist who is an expert in cancer will carry out two evaluation sessions to verify that they meet all the inclusion criteria. Once evaluated, randomization will be carried out by an independent researcher who is blind to the evaluation of the participants. At all times, the randomization sequence will be concealed from the clinicians participating in the study. The evaluation will be carried out by independent evaluators who are blind to the experimental conditions. Subsequently, each participant will begin their group intervention in the condition to which they have been assigned. Participants will not receive any other psychological or psychiatric treatment during this study. When the psychotherapy is over (MCP or CBT), the evaluation will be carried out again. A follow-up will be carried out at 1 month, at 3 months, and at 6 months. The evaluation will be carried out online before and after finishing the treatment and in the follow-ups. All the interventions will be performed by clinical psychologists or general health psychologists with a Master's degree and previous training in the application of the programs. All the interventions will be carried out through online video conferences in both treatment conditions.

### Ethics

The study involves clinical experimentation with human participants. Researchers adhere to the Helsinki Convention and the Madrid Declaration of the World Psychiatric Association on clinical research. This project has been approved by the Ethics and Research Committee of the Valencian Institute of Oncology Foundation (CEIM: 2019–17). The study was registered with Clinicaltrials.gov as NCT05197348. All participants will be volunteers and give their informed consent to participate in the study. All eligible participants will receive oral and written information about the study and the two intervention modalities. Specifically, they will be informed that they can leave the study at any time without any explanation, and that this decision will not affect the continuation of their usual treatment at the Valencian Institute of Oncology. The selection and evaluation of the participants will be carried out by a clinical psychologist who is blind to the condition assigned to the participants. The intervention will be carried out by two psychologists who specialize in cancer. In addition, it should be noted that the protocols for action and custody of the information followed in the Valencian Institute of Oncology, where the participants will be recruited and the interventions will be carried out, comply with all the requirements of the LOPD (Organic Law 15/1999, of December 13, 2018). In addition, based on the existing knowledge in this field, we have not found any risks to the participants. However, any important clinical change that involves some type of risk will not only imply the participant's termination in the study, but also his/her referral for study and specialized care. The evaluation protocol described above is composed of standardized and risk-free instruments for the participants (interviews and questionnaires). The intervention protocols are based on empirically validated treatments designed and developed by personnel with extensive knowledge and experience in this field. For ethical reasons, participants in the CBT condition will be offered the opportunity to receive the MCP program, if they so desire, even if the study has already ended.

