### Data Analyses

For data analysis, the Consort guidelines will be followed. Prior to analyzing whether MCP was more effective than CBT, we will verify that the two experimental conditions are similar in all the sociodemographic variables, such as age, sex, marital status, and education. In addition, we will verify that the two conditions are similar in terms of the percentage of participants who have received chemotherapy, radiotherapy, and surgery. To do so, we will use comparison of means (Student's t) for the continuous variables and chi square for the categorical variables. Moreover, the intention-to-treat principle will be used when analyzing pre- and post-treatment data and at the 6-month follow-up, using mixed-effects models with full information and maximum likelihood estimation. This method has been recommended due to its flexibility in handling missing data (51). To complement the MANOVA results and *post hoc* comparisons, effect sizes will be calculated using the standardized mean difference proposed by Cohen (52). These effect sizes will be calculated to assess changes within and between groups, all based on a pooled standard deviation. MANCOVAS will be carried out to find out if there are differences in the participants' response to the two experimental conditions depending on the type of medical treatment administered (surgery, chemotherapy, or radiotherapy), the stage of the cancer before the start of medical treatment, and whether the patient has a relapse during the psychological treatment. Moderation and mediation analyses will be performed to investigate possible mediators of change during treatment, such as meaning in life or coping style. Although per-protocol analyses (only analyses of data from participants who complete the treatment) suffer from selection bias, they will also be conducted because they allow conclusions to be drawn about the maximum efficacy of the intervention in participants who are fully compliant with treatment. However, when the trial is completed, the analytical methodology for controlled clinical trials will be reviewed before analyzing the data to select the most appropriate analytical procedures.

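### On its natural reading, the Ethics section ends study participation after a clinical change involving risk, so later outcomes are avoidably lost to the 6-month intention-to-treat analysis; the likely effect is small

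*Protocol article*

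**What the plan says.** The rule stands in the protocol article, Ethics. When a participant has a serious clinical change that carries risk, the stated consequence is "termination in the study, but also his/her referral for study and specialized care". It is not limited to the therapy sessions. Earlier in the same section, participants are told that "they can leave the study at any time without any explanation", where the study plainly means the trial as a whole. The section also states that "based on the existing knowledge in this field, we have not found any risks to the participants" and describes the evaluation battery as "composed of standardized and risk-free instruments for the participants (interviews and questionnaires").

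Procedure places all assessments online and schedules follow-up at 1, 3 and 6 months. It also bars any outside psychological or psychiatric care while the study runs. Measures has both arms complete every outcome at five time points.

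Data Analyses commits that "the intention-to-treat principle will be used when analyzing pre- and post-treatment data and at the 6-month follow-up", with mixed-effects models fitted by maximum likelihood: "This method has been recommended due to its flexibility in handling missing data". Of the standardised mean differences it says: "These effect sizes will be calculated to assess changes within and between groups". It also plans MANCOVAs by, among other factors, relapse during the psychological treatment. Sample Size allows for 30% dropout.

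**The concern.** An intention-to-treat analysis to 6 months needs the outcomes of people who got worse as much as those of people who did well. Ordinary dropout is the participant's own decision. This loss would be imposed by the protocol, triggered by worsening, and avoidable, because the questionnaires are online and could continue after referral.

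The maximum-likelihood model keeps the scores obtained before the event, and it is valid if the missing scores are predictable from those. A new deterioration is by nature not fully predictable from earlier scores, so the correction is only partial. At stake are the within-arm effect sizes, which would look too good, and to a lesser degree the MCP-CBT contrast. If a cancer relapse counts as such a change, which the text does not settle, the planned analysis by relapse would also lose the later outcomes it needs.

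**Working it through.** **Reading the text.** Three things favour the wider reading: the object of the sentence is the study, the same section uses that word for the whole trial, and the ban on outside treatment in Procedure could not be met by a participant referred for psychological or psychiatric care who stayed in. One thing points the other way: an analysis by relapse during therapy presupposes that at least some clinically deteriorating participants are still assessed.

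**Nearest stated figure.** The document gives no figure for this rule. Its sample size of 45 per arm (d = 0.60, two-sided alpha 0.05, power 0.80) reproduces: the two-sample t-test needs 44.6, and 45 gives power 0.804. If terminations came on top of the planned loss, 1, 2 or 3 fewer per arm would lower power to 0.795, 0.785 or 0.776. If they fall within the 30% already allowed for, nothing changes.

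**Inputs for the bias calculation**
- 59 randomised per arm and a true effect of 0 or 0.60 SD (Sample Size).
- Correlation 0.70 between baseline, post-treatment and 6-month scores. This is the one-month retest value for MLQ Presence (Measures of Primary Outcomes), used as a proxy.
- Termination rate in the CBT arm: not given. Assumed 1%, 2%, 5% and 10%, that is 59 × rate = 0.6, 1.2, 3.0 and 5.9 participants.
- Link k between trigger and 6-month score: assumed 0.5 (moderate) or 1 (strong: the trigger is the score itself).

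**Method.** Simulation with 2,000,000 per arm and all SDs 1. The 6-month score Y is lost when k·Y + √(1 − k²)·noise falls below the CBT arm's 1%, 2%, 5% or 10% quantile, with the same threshold in both arms. The likelihood estimate under missing at random regresses the observed 6-month scores on arm, baseline and post-treatment score, then averages the predictions over everyone randomised. Bias is that estimate minus the full-data mean.

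| CBT loss | Within-arm bias, equal loss, k = 0.5 | same, k = 1 | Contrast bias at d = 0.60, k = 0.5 | same, k = 1 |
|---|---|---|---|---|
| 1% | 0.006 | 0.012 | −0.003 | −0.009 |
| 2% | 0.011 | 0.022 | −0.005 | −0.017 |
| 5% | 0.024 | 0.052 | −0.010 | −0.035 |
| 10% | 0.043 | 0.099 | −0.016 | −0.060 |

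With d = 0, loss is equal in the two arms and the contrast bias is 0.000 throughout.

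**Event during therapy.** The table keeps the post-treatment score. If that is lost too, then at 10% loss the strong-link figures become about 0.116 (within arm, equal loss) and −0.071 (contrast at d = 0.60). The moderate-link figures become about 0.05 and −0.02.

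**Referral helps.** If outside care raises the later scores of those terminated by 0.5 SD, the strong-link contrast bias at d = 0.60 (post-treatment score kept) shrinks to −0.005, −0.009, −0.016 and −0.025. The moderate-link bias is within 0.006 SD of zero.

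**Cruder check, without the model.** Bias = difference in termination rate × unexplained shortfall. From 0.01 × 0.5 = 0.005 SD to 0.05 × 1.0 = 0.05 SD.

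**Scale.** Completers per arm: 59 × 0.70 ≈ 41. Standard error of the contrast: √(2/41) = 0.221 SD, or √(2/41 × (1 − 0.70²)) = 0.158 SD adjusted for baseline. The moderate-link bias at 10% loss is 0.016/0.158 = 0.10 of that, or 0.02/0.158 = 0.13 without the post-treatment score. The most extreme case shown is 0.071/0.158 = 0.45.

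**The case against.** The strongest reply is that one loosely worded ethics assurance carries the point. A clinician's safety stop is not the same event as a participant's own exit, the sentence does not say that assessments cease, and the planned analysis by relapse suggests that some who deteriorate stay in follow-up. This stands as a limit on certainty. It does not remove the point, since the natural reading is still that participation ends and staff could follow it that way.

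A second reply is that a journal article need not describe follow-up after discontinuation. That is right about silence, but here the article states a rule, and no analysis plan can recover scores that were never collected.

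A third is that ending participation fits the ban on outside treatment, and that scores after referral mix in other care. This is fair. It is a choice about what to estimate, and intention-to-treat ordinarily accepts such scores, but it means that Procedure must be reconciled with any rewording.

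A reader might go further and infer that the rule contradicts the visit schedule or the mixed model. It does not: both can coexist with losses, and Sample Size expects 30% dropout. A reader might also infer that the rule could manufacture an MCP advantage. Under one common trigger it does the reverse: if MCP does better, fewer MCP participants are removed and its advantage is understated.

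**Conclusion.** The point holds as a minor one. On its natural reading the Ethics section discards, by rule, later outcomes of participants who deteriorate, and these belong in the 6-month intention-to-treat analysis.

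The size is small: under a moderate link and 1% to 10% loss, about 0.006 to 0.05 SD on within-arm change and 0.003 to 0.02 SD against MCP at a true effect of 0.60. At 10% loss with a strong link and the post-treatment score also gone, it is about 0.12 and 0.07 SD. Equal loss leaves the contrast unbiased. None of this threatens the main comparison or changes the sample size.

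These figures rest on assumed event rates and links, a borrowed correlation and a trigger applied alike in both arms. The document reports no known risks, so the low end of the range is the more plausible. Because the trigger is clinical risk, the link is probably weaker for the primary meaning scores than for anxiety, depression or hopelessness.

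**What to change.** Reword Ethics so that an important clinical change involving risk ends the study treatment and triggers referral, while the online outcome questionnaires continue at the remaining visits if the participant consents and is clinically able. Analyse everyone as randomised. Add to Procedure that the ban on outside psychological or psychiatric treatment does not end outcome assessment for participants referred this way. If only stopping therapy was meant all along, the same wording settles it.

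The cost is two short changes of text, made by amendment because the study is described as ongoing, and some questionnaire burden on a few referred participants: up to ten instruments at up to four remaining visits. Their later scores will reflect outside care, which should be acknowledged when reporting. Referral and the right to withdraw are unaffected. A sensitivity analysis that shifts the missing scores of anyone still lost this way, for example by 0.5 and 1 SD, is optional and can be left to the SAP.

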### Interventions

#### Meaning-Centered Group Psychotherapy

To carry out the adaptation of the Manualized Meaning-Centered Group Psychotherapy (MCP) group format for patients with advanced cancer (32) to Spanish, we used the ecological validity model (EVM) (33) as a framework for the cultural adaptation of MCP to respond to the needs of the Spanish population with cancer. According to the EVM, to adapt an intervention for a new cultural group, seven dimensions need to be addressed: language, context, persons, metaphors, concepts, goals, and methods. We first carried out a translation of the original MCP program from English to Spanish. The translation was performed by two bilingual clinical psychologists who are experts in meaning-focused psychotherapy; this translation was supervised by a bilingual editor with expertise in clinical psychology. A feasibility study (in preparation) with 12 participating cancer survivors was conducted by two clinical psychologists who are experts in cancer. Finally, we tested the understanding, acceptance, and feasibility of the Spanish version of the MCP with a qualitative interview and questionnaires. The intervention lasts 2 months and includes 8 sessions that follow a 2-h group format on a weekly basis. We will follow the manualized MCP for patients with advanced cancer (32). The MCP program is divided into 8 sessions:

Session 1: Concepts and Sources of Meaning.Introductions; review of concepts and sources of meaning; Meaningful Moments experiential exercise; homework is to read Man's Search for Meaning and reflect on the Session 2 experiential exercise.Session 2: Cancer and Meaning.Discussion of sense of identity before and after cancer diagnosis; Who am I? experiential exercise; homework is to reflect on the Session 3 experiential exercise.Session 3: Historical Sources of Meaning (Past Legacy).Discussion of life as a legacy that has been given (past); Historical Sources of Meaning-Past experiential exercise; homework is to reflect on the Session 4 experiential exercise.Session 4: Historical Sources of Meaning (present and future).Creation of lifeline. Own legacy development. Exercises: Reflection on the autobiography (in session and at home). Evaluate how situations are approached, objectives they had and that have been achieved. Explore a future legacy.Session 5: Attitudinal Sources of Meaning: Encountering Life's LimitationsDiscussion of confronting limitations imposed by cancer, prognosis, and death; Encountering Life's Limitations experiential exercise; introduction to Legacy Project; homework is to reflect on the Session 6 experiential exercise.Session 6: Creative Sources of Meaning: Engaging in Life Fully.Discussion of creativity, courage, and responsibility; Creative Sources of Meaning experiential exercise; homework is to reflect on the Session 7 experiential exercise.Session 7: Experiential Sources of Meaning: Connecting with LifeDiscussion of experiences as sources of meaning, such as love, nature, art, and humor; Love, Beauty, and Humor experiential exercise; homework is to complete the Legacy Project for presentation in Session 8.Session 8: Transitions: Reflections, and Hopes for the Future.Review of sources of meaning as resources, reflections on lessons learned; Hopes for the Future experiential exercise; goodbyes.

#### Cognitive Behavioral Psychotherapy

The intervention lasts 2 months and includes 8 sessions that follow a 2-h group format on a weekly basis, with the following sessions (21):

Session 1: Presentation of psychotherapy, establishing the goals of psychotherapy. Presentation of the participants. Updated information about psychological consequences of cancer.Session 2: Increase in enjoyable activities. Behavioral activation. Progressive muscle relaxation training. Slow breathing training.Session 3: Cognitive model of coping with cancer. ABC model. Psychoeducation on negative thoughts. Training in detecting negative thoughts. Presentation of cognitive distortions.Session 4: Training in cognitive restructuring techniques.Session 5: Training in problem-solving skills.Session 6: Being aware of our own needs. Self-care. Assertiveness skills training.Session 7: Setting goals for the future.Session 8: Summary, relapse prevention, and end of psychotherapy.

### Measures

After reviewing the literature, an evaluation protocol was designed that includes the main instruments that have been commonly used by authors working in this field (29), as well as some additional instruments that we consider relevant to the hypotheses proposed. In all cases, the Spanish validations of the assessment instruments will be used; if they do not exist, the validations will be carried out by the researchers of this study. Participants in both treatment conditions will complete all primary and secondary outcome measures at five time points: before and after treatment and at 1-month, 3-month and 6-month follow-ups.

#### Measures

Data on demographic variables: Age, gender, educational level, marital status, cancer diagnoses, cancer treatment, mental diagnoses.

##### Measures of Primary Outcomes

*Meaning in Life Questionnaire [MLQ*
*(**34**)**]*. The MLQ is a self-reported questionnaire made up of 10 items, and it was developed to assess the two main dimensions of meaning in life: presence and search for meaning in life. The items are rated on a 7-point scale ranging from 1 (absolutely false) to 7 (absolutely true). The factors of Presence and Search were correlated (*r* = −0.19), and internal consistency was good for Presence (0.86) and Search (0.87). One-month test-retest reliability coefficients were 0.70 for Presence and 0.73 for Search.

*The Multidimensional Existential Meaning Scale [MEMS*
*(**35**)**]*. The MEMS assesses the MiL dimensions: Comprehension, purpose, and mattering, with a total of 15 items (e.g., “My life makes sense”; “I have overarching goals that guide me in my life”; “I understand my life”; “I know what my life is”). Likert type responses are given on a 7-point scale (1 = Very strongly disagree; 7 = Very strongly agree). The three MEMS subscales showed adequate internal consistency: Comprehension (ϖ = 91), Purpose (ϖ = 92), and Mattering (ϖ = 86).

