As we have seen, MCP has been shown to be effective in improving meaning in life and quality of life and reducing distress in people with cancer. However, it is important to emphasize that all the studies mentioned above on the application of MCP in cancer patients have been carried out in Anglo-Saxon samples and have mainly focused on patients with a diagnosis of cancer in III-IV stages. The construction of meaning, vital goals, responsibility, sources of meaning, and the comprehension and acceptance of these constructs depend on cultural, social, and religious factors, etc. (19). There are studies that indicate that the construction of meaning and growth in the face of adverse situations is different for Anglo-Saxon and Spanish populations. For example, a previous study found that, in the American sample, the presence and search for meaning were moderately and negatively associated, whereas these two factors were uncorrelated in the Spanish population (20). Therefore, it is necessary to adapt and verify the efficacy of MCP in populations that speak languages other than English, such as Spanish and to test the efficacy of MCP in patients with an early stage I–III diagnosis of cancer.

Another psychotherapy that has been found to be effective in participants with cancer is cognitive behavioral therapy (CBT). The adaptation of CBT to participants with cancer is a comprehensive cognitive-behavioral model based on Beck's therapy for depression. The cognitive model of adjustment to cancer states that the patient's assessment, interpretation, and evaluation of cancer is what will determine his/her emotional and behavioral reaction. CBT has been considered a psychological behavioral therapy that, when specifically delivered to cancer patients, focuses on managing emotions, cognitions, problem-solving, relaxation, and assertiveness, and on improving coping with cancer (21). This therapy has been found to be effective in improving anxiety, depression, helplessness, fatalism, anxious preoccupation, and coping (22). CBT has also been found to improve the change in quality-of-life associated with distress due to medical treatments or to adjustment after the disease is treated (23) and lead to greater adaptability to cancer, thus reducing vital anguish (24).

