### Sample Size

The sample size for this study was generated from effect sizes found in other studies on MCP in participants with cancer, mainly meta-analyses. Dietrich (29) found medium effect sizes for meaning in life (*d* = 0.81), Quality of life (*d* = 0.60), anxiety (*d* = −0.47), and depressive symptoms (*d* = −0.50). These effect sizes are consistent with other studies on MCP in psychological treatments for other mental disorders, such as a meta-analysis by Vos et al. (12) on existential psychotherapies. Based on the results of these studies, we expect an effect size of 0.60 because the study design consists of two experimental groups. To calculate the sample size, we used the G^*^Power 3.1 software (30), taking into account an alpha of 0.05 and a statistical power of 0.80 on a two-tailed *t*-test. We need a sample size of 90 participants (45 participants per condition) to reach an effect size of 0.60 for meaning in life. Finally, we have considered possible sample loss during the treatment program, and based on studies of interventions with MCP, we expect a 30% dropout rate (9). Therefore, taking this outcome into account, our study requires a total sample size of 118 participants (59 participants per experimental condition).

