The third objective of this proposed study will be to analyze whether the changes produced in the MIL dimensions (presence, search, comprehension, purpose, and mattering) predict the changes in anxiety, depression, quality of life, etc. In this study, we will use multidimensional measures of meaning to assess change in meaning in life. The MEMS (35) will allow us to evaluate the three dimensions of meaning (comprehension, purpose, and mattering), and the MLQ (36) will allow us to include two other dimensions (presence, search). Evaluating the effectiveness of MCP with multidimensional measures will allow us to find out whether it is effective for all the dimensions of meaning or, on the contrary, produces a change in one dimension (e.g., presence) but not in another (e.g., search). In addition, we will be able to verify which dimension of meaning best predicts the change in the patients' clinical measurements.

Another contribution of this proposed study is the application of MCP through videoconference. To the best of our knowledge, there are no studies on the efficacy of PCM *via* videoconference. This would allow us to take MCP to people who live in places where there are no psychotherapists, so that a greater number of people from very distant places could receive treatment. Some studies have described the advantages of online psychosocial interventions (55), such as compensating for geographical barriers and saving travel time (56). Currently, the number of psycho-oncological pilot studies of online interventions through videoconference in psycho-oncology is increasing. Results have highlighted participant engagement and effectiveness (57, 58). Moreover, a recent randomized control study (59) found similar effectiveness of both face-to-face and online psychotherapy for patients with a diagnosis of cancer with cancer distress. Finally, we must emphasize that we are going to carry out a follow-up at 6 months to confirm whether the results obtained after treatment are maintained, improve, or worsen in both treatment conditions.

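### The primary outcome is two instruments with five subscales and no order among them, but the sample size fits only one test of an unidentified meaning-in-life score

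*Protocol article*

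**What the plan says.** The section Measures of Primary Outcomes in the protocol article names two instruments. Of the MLQ it says that "it was developed to assess the two main dimensions of meaning in life: presence and search for meaning in life". Of the second it says "The MEMS assesses the MiL dimensions: Comprehension, purpose, and mattering, with a total of 15 items". Neither is given a total score, and no subscale is put first.

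The Sample Size section treats meaning in life as one quantity. The calculation was made "taking into account an alpha of 0.05 and a statistical power of 0.80 on a two-tailed" t-test, and its result is: "We need a sample size of 90 participants (45 participants per condition) to reach an effect size of 0.60 for meaning in life". The section does not say which instrument, subscale or time point this refers to.

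The Introduction and the Discussion list the same five dimensions: presence, search, comprehension, purpose and mattering. The Discussion says the multidimensional measures will show whether MCP works on all of them or "produces a change in one dimension (e.g., presence) but not in another (e.g., search").

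Hypothesis (a) in the Introduction expects both arms to improve on meaning in life after the intervention, and MCP to improve more. Under Measures, primary and secondary outcomes are collected at five time points. Data Analyses covers pre-treatment, post-treatment and 6 months with mixed-effects models, and mentions MANOVA and post hoc comparisons in passing.

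**The concern.** The two sections do not fit together. The stated alpha and power hold for one comparison of one score, but the primary outcome section supplies at least two candidates and, on its own description, five. If several are each tested at 0.05, the error rate behind the 45 per arm no longer applies to the primary conclusion. If alpha is divided among them, the stated power no longer applies.

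MLQ Search adds a separate difficulty. The hypothesis speaks of improving and the Discussion of a change, but nowhere is it said whether a higher or a lower Search score is the better result. Presence gives no guide. The MLQ description reports r = -0.19 between the two factors, and the Introduction reports them as uncorrelated in the Spanish population, which is the population of this trial. A between-arm difference on Search alone could not be read as benefit or harm from what is written.

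**Working it through.** **Inputs from the documents.** d = 0.60, two-sided alpha 0.05, power 0.80, t-test, 45 evaluable per arm (Sample Size); two instruments with 2 + 3 = 5 subscales (Measures of Primary Outcomes).

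**Assumptions.** Correlations between subscales, other than the two Presence–Search statements, are not given in the documents and are varied below. The error rates take MCP and CBT as equal on every score.

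**1. The plan's own figure.** Normal approximation: n per arm = 2(1.960 + 0.842)² / 0.60² = 43.6, so 44. The noncentral t calculation gives 44.6, so 45 per arm and 90 in total, with power 80.4%. The stated figure reproduces as one test at an undivided 0.05.

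**2. At least one false-positive primary result, each score tested at 0.05 two-sided.**
- Two independent scores (one per instrument): 1 − 0.95² = 9.75%.
- Five independent scores: 1 − 0.95⁵ = 22.6%.
- Five scores with a common correlation, by simulation: 20.9% at 0.3, 18.3% at 0.5, 14.8% at 0.7.
- Search uncorrelated with the other four, which correlate 0.5 or 0.7 with each other: 19.9% or 17.4%. This pattern is closer to what the Introduction reports for Presence and Search in Spain.

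**3. The same, counting only results that favour MCP.**
- One score: 2.5%.
- Five independent scores: 1 − 0.975⁵ = 11.9%.
- Five independent scores, with a Search difference counted in either direction: 1 − 0.975⁴ × 0.95 = 14.1%.

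**4. What dividing alpha would cost (d = 0.60 on each score).**

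| Primary scores | Alpha each | Power per score at 45 per arm | Evaluable per arm for 80% |
|---|---|---|---|
| 1 | 0.05 | 80.4% | 45 |
| 2 | 0.025 | 71.4% | 55 |
| 5 | 0.01 | 58.6% | 67 |

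**5. If success required all five at 0.05.** Power at 45 per arm would be about 46% to 61% for common correlations of 0.3 to 0.7, with d = 0.60 on every subscale.

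So neither dividing alpha over two or five scores nor requiring all five gives the stated 80% power at 45 per arm.

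**The case against.** - **Five primaries is a reading.** The article names two instruments, not five endpoints. That is fair, and on two scores the inflation is 9.75% rather than 22.6%. But no total score is defined for either instrument, and the Discussion commits to reading each dimension. If a composite was meant, the primary variable is still undefined.
- **No success rule is written.** A reader might infer that superiority on any one of five subscales, at post-treatment or at 6 months, would count as success; ten such tests would carry a false-positive chance of about 30% under assumed correlations. The documents do not support this. No section states such a rule, hypothesis (a) places superiority after the intervention, and the Discussion gives the 6-month follow-up the role of showing whether results last. The Discussion's wording on dimensions describes a profile of effects.
- **The 22.6% counts errors in both directions.** Correct. For a claim that MCP is better, the comparison is 11.9% against 2.5%.
- **Multiplicity control may sit in a separate SAP.** The adjustment method may well be there. The choice of primary outcome and its match to the sample size are fixed in this article, and these disagree. The end of Data Analyses also leaves the selection of procedures until the trial is complete.
- **The MANOVA could act as a joint test.** The article does not say which outcomes enter it, and mixed-effects models are the stated intention-to-treat analysis. A significant omnibus test also does not control error across unadjusted follow-up tests when only some of the null hypotheses are false.
- **Search.** A reader might infer that a difference in either direction will be claimed as benefit, or that r = -0.19 belongs to a particular national sample. The first is conjecture. For the second, the MLQ description names no population, and the population contrast in the Introduction comes from a different cited study. What stands is that the direction of improvement is not stated.

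**Conclusion.** The point holds in this form: the stated alpha and power fit a single primary score that the article never identifies. The size depends on how many scores are tested and how they correlate. Unadjusted, the chance of at least one false-positive primary result is 9.75% for two independent scores and 22.6% for five, or about 15% to 21% for five at assumed common correlations of 0.7 to 0.3. In favour of MCP only, it is 11.9% for five independent scores. Bonferroni over five would leave about 59% power per scale at 45 per arm. These figures show what follows if each score is tested at 0.05, which the document does not say will be done. A Search difference cannot serve as evidence of superiority until its favourable direction is defined.

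**What to change.** Before data are analysed, state in the protocol, the SAP and the registry entry:
- The one primary score and time point to which the d = 0.60 calculation refers. MLQ Presence at post-treatment is an example that matches the timing in hypothesis (a). Nothing in the article ties 0.60 to Presence, so the choice is the sponsor's.
- That the remaining meaning subscales and the 6-month result are secondary, tested in a fixed order or by Holm.
- That MLQ Search is reported descriptively or as exploratory, and not as evidence of superiority.

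This keeps alpha at 0.05 and the target of 45 evaluable per arm, and costs only wording. The downside is that fewer outcomes can be called primary. If the sponsor wants more than one primary score, alpha has to be divided and the sample size recalculated: with Bonferroni, 55 evaluable per arm for two scores or 67 for five.
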